### 2.8 Secondary outcomes

COVID-19’s effect on systemic micro- and macrovascular endothelial function (LSCI, FMD) will be measured by trained investigators at baseline and 18-month follow-up.Patients will be cognitively assessed by *n*-back working memory paradigm and NIH Toolbox Cognitive Battery to determine whether COVID-19 contributes to decreased fluid and/or crystalized cognitive performance. Patients will also complete select questionnaires from Emotion Battery (Emotional Support, Friendship, Loneliness, Perceived Hostility, Perceived Rejection, and Instrumental Support questionnaires) and Adverse Childhood Experience questionnaire to determine current state of social support/interaction and traumatic events during childhood, both of which are known to exacerbate and contribute to cognitive impairment [44,45]. All cognitive, emotional, and adverse childhood experience assessments will be performed at baseline and 18-month follow-up.Circulating levels of pro-inflammatory cytokines, antioxidant capacity, and vascular disease markers will be measured at baseline and 18-month follow-up by trained investigators to determine the long-term effects of COVID-19 on systemic inflammation, oxidative stress, and biomarkers of endothelial dysfunction. A registered nurse will perform blood draws from patients (~40 ml) and trained investigators will process blood and store in -80° freezer until ready for quantification of pro-inflammatory cytokines and vascular disease markers, and antioxidant capacity by magnetic bead-based multiplex assay and hydroxyl radical antioxidant capacity (HORAC) activity assay, respectively.

### 2.9 Study variables

All variables included in the study are represented in **Table 1**, and separated based on level of measurement (continuous, ordinal, discrete, binary). Below, the variables are described for each specific aim, as mentioned in the *Study aims* section.

**Table 1 pone.0289508.t001:** Summary of variables for study aims.

Variable	Method of Measurement	Operational definition	Level of measurement
**NVC**	fNIRS	Change in relative HbO concentration in cortical small vessels during cognitive task	Continuous
**Band-limited power**	EEG	Amount of electrocortical activity in distinct frequency bands during cognitive task	Continuous
**Retinal arteriolar function**	DVA	Retinal arteriolar response to flickering light stimulus (NVC stimulus)	Continuous
**Microvascular endothelial function**	LSCI	Small vessel hand perfusion following the release of 5-minute occlusion	Continuous
**Macrovascular endothelial function**	FMD	Percent change in brachial artery diameter from baseline to release of 5-minute occlusion	Continuous
**Pro-inflammatory cytokine levels**	Magnetic bead-based multiplex assay	Quantified fluorescence intensity in pro-inflammatory cytokine levels	Continuous
**Endothelial dysfunction biomarkers**	Magnetic bead-based multiplex assay	Quantified fluorescence intensity in cardiovascular disease panel markers	Continuous
**Antioxidant capacity**	HORAC activity assay	Fluorescence decay curve: time until complete decay of fluorescent probe	Continuous
**Fluid intelligence**	NIH Toolbox	Individual and categorical T score based on cognitive test responses	Continuous
**Crystalized Intelligence**	NIH Toolbox	Individual and categorical T score based on cognitive test responses	Continuous
**Emotion Score**	NIH-Toolbox	Individual T-score based on normative population data	Continuous
***n*-back working memory performance**	n-back	Percentage of correct responses and reaction time during *n*-back blocks	Continuous
**Blood pressure**	AD instruments	Blood pressure recorded during visits	Continuous
**Time since SARS-CoV-2 Infection**	Demographic	Duration from COVID-19 diagnosis to Visit 1	Continuous
**Age**	Demographic	Age (in years) of participants at each visit	Discrete
**Fazekas scale**	MRI	WMH burden (0–3) periventricular and deep	Discrete
**MoCA**	Demographic	Montreal cognitive assessment score (0–30)	Discrete
**ACE score**	ACE questionnaire	Adverse childhood experience questionnaire, scored 1–10 with a score of 10 having high ACE	Discrete
**Comorbidities**	Demographic	Past medical history and/or ongoing medically controlled for conditions	Nominal
**SARS-CoV-2 Variant**	Demographic	Estimated variant based on time (month and year) patient was infected with SARS-CoV-2	Nominal
**Vaccination History**	Demographic	Number of doses, vaccine manufacturer	Nominal
**Education**	Demographic	Highest level of education obtained	Ordinal
**Progression of MCI to dementia**	Clinical diagnosis	Use of neurocognitive screening (e.g., MoCA, clinical dementia rating) and final adjudication made through consensus management	Binary
**COVID-19 status**	*Previously confirmed COVID-19 history	COVID-19 positive or COVID-19 negative	Binary
**Sex**	Demographic	Male or female	Binary

Note. Neurovascular coupling (NVC), Functional near-infrared spectroscopy (fNIRS), Oxy-hemoglobin (HbO), Electroencephalography (EEG), Dynamic retinal vessel analysis (DVA), Laser speckle contrast imaging (LSCI), Flow mediated dilation (FMD), Hydroxyl radical antioxidant capacity assay (HORAC), White mattery hyperintensity (WMH), Montreal cognitive assessment (MoCA), Mild cognitive impairment (MCI), Adverse childhood experience (ACE).

* Indicates COVID-19 was confirmed by PCR or serologic testing.

■ Aim 1 variables will be used to address whether history of SARS-CoV-2 infection impairs systemic endothelial function and NVC response in patients with MCI. Variables included in this Aim are: NVC, band-limited power of brain waves, retinal arteriolar function, microvascular endothelial function, macrovascular endothelial function, endothelial dysfunction biomarkers, pro-inflammatory cytokine level, antioxidant capacity, COVID-19 status, SARS-CoV-2 variants, time since infection, and vaccination history.■ Aim 2 variables will be used to address whether MCI patients with history of COVID-19 have impaired fluid cognitive function compared to MCI patients with no COVID-19 history. Variables included in this Aim are: *n*-back working memory performance, fluid intelligence, COVID-19 status, SARS-CoV-2 variants, time since infection, and vaccination history.■ Aim 3 variables will be used to address whether history of COVID-19 in patients with previously diagnosed MCI contributes to progression to dementia, and whether impaired NVC associates with increased progression to dementia. Variables included in this Aim are: NVC, retinal arteriolar function, band limited power of brain waves, COVID-19 status, SARS-CoV-2 variants, time since infection, vaccination history, and progression of MCI to dementia.■ Aim 4 variables will be used to address whether history of COVID-19 in MCI contributes to increased burden of WMH, and whether elevated level of WMH burden contributes to increased progression of MCI to dementia. Variables included in this Aim are: Fazekas scale, COVID-19 status, SARS-CoV-2 variants, time since infection, vaccination history, and progression of MCI to dementia.

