**Fig 1 pone.0289508.g001:**
[figure not shown]
Timeline for study design and investigative measurements. (Top) Timeline of prospective longitudinal study. Visit 1 and Visit 2 (red) includes: Physiological and cognitive assessments and blood draw. (Bottom) Investigative measures including physiological and cognitive assessments and circulating factors recorded at Visit 1 and 2 (red) and baseline MRI recorded at diagnosis of MCI prior to COVID-19 pandemic, and 18-month follow-up MRI (black). Red arrows indicate deep WMH, and orange arrows indicate periventricular WMH. Abbreviations: White matter hyperintensity (WMH), Functional near-infrared spectroscopy (f-NIRS), Electroencephalography (EEG), Dynamic retinal vessel analysis (DVA), Laser speckle contrast imaging (LSCI), Flow mediated dilation (FMD).

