### 2.7 Primary outcome

The primary outcome of interest is whether COVID-19 contributes to the progression of MCI to dementia through impairment of NVC response, and promotion of white matter damage. Diagnosis of MCI and progression to dementia will be made clinically through the OUHSC Department of Neurology. Trained investigators will perform NVC measurements (fNIRS, electroencephalography [EEG], DVA) at baseline and 18 months follow-up. Burden of white matter damage (WMH) will be neuroradiologically assessed by the clinical neurology and neuroradiology team at baseline (at diagnosis of MCI prior to COVID-19 pandemic) and 18-month follow-up.

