### 2.10 Data collection process

Patients who have consented to the study are interviewed for demographic information (sex, age, race education), COVID-19 history (symptoms during infection, and symptoms without confirmed infection), COVID-19 vaccine history, medical history (oncological, genitourinary, gastrointestinal, respiratory, endocrine, neurological, cardiovascular, musculoskeletal, and psychological conditions), screened for DVA (eye surgery history, photosensitive epilepsy, glaucoma, allergies to tropicamide), and social history (previously or current use of tobacco, alcohol, and recreational drugs, and adverse childhood experiences). Medication list is obtained from all patients, and common age-related conditions (i.e., hypertension, diabetes) must be pharmacologically controlled. All patients enrolled have baseline MRI data with neuroradiologic report at MCI diagnosis. Every 6 months patients have repeat neurocognitive screening and evaluation through OUHSC Department of Neurology faculty to identify if patients have progressed from MCI to dementia. Physiologic, circulating factors, and cognitive data is obtained from patients at visit one and at 18-month follow-up. Patients are scheduled through the Department of Neurology for a second MRI to obtain neuroradiologic report at 18-month follow-up after visit one.

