### 4.2 Longitudinal data analysis

Continuous data will be analyzed by 2-way ANOVA and categorical with Chi-square or Fisher’s exact test for within and between groups (COVID+ vs COVID-) comparison. Effect size will be calculated for all within and between group analyses. For **primary outcome** analysis, we will determine whether COVID-19 related impairment in NVC and increases in WMH burden contributes to progression to dementia. Progression to dementia within and between groups will be analyzed and multivariate analysis will be conducted to determine the effect of COVID-19, NVC (i.e., fNIRS), change in WMH burden, and interaction between group (COVID+, COVID-) and NVC and WMH burden on progression to dementia. **Secondary outcome** measures (i.e., FMD, LSCI, EEG, DVA, NIH Toolbox, circulating factors) will be compared within and between groups. Demographic variables, COVID-19 variants, duration of COVID-19 and vaccination will be assessed as factors for progression to dementia through logistic regression. **Exploratory analyses** will include univariate analysis of all demographics, physiologic, cognitive, and structural variables, and their effect on progression to dementia. All values with a p value <0.2 will be included in a multivariate model to assess their contribution to progression to dementia. We expect that several variables will have p value <0.2; therefore, we will conduct dimensionality reduction before adding into the model to assess variables which have strongest correlation with principal components. The limitation for the multivariate model will be sample size, however this is not a primary outcome measure and is used to generate new hypotheses to test in future studies.

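### Time from MCI diagnosis to Visit 1 is missing from the variable list and from the primary progression model, so differing MCI durations and differing WMH-change intervals go unadjusted

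*Protocol article*

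**What the plan says.** All references are to the protocol article.

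- **Variable list.** Section 2.9 opens with "All variables included in the study are represented in" Table 1. The only duration in that table is time since infection, defined as "Duration from COVID-19 diagnosis to Visit 1", which exists only for COVID+ patients. Time since MCI diagnosis has no row.
- **Aim lists.** Section 2.9 says that "Aim 3 variables will be used to address whether history of COVID-19 in patients with previously diagnosed MCI contributes to progression to dementia". Besides the NVC measures, the Aim 3 list holds "COVID-19 status, SARS-CoV-2 variants, time since infection, vaccination history, and progression of MCI to dementia". Aim 4 has the same items with the Fazekas scale in place of the NVC measures. Neither list has MCI duration.
- **Primary model.** Section 4.2 says "multivariate analysis will be conducted to determine the effect of COVID-19, NVC (i.e., fNIRS), change in WMH burden", plus interactions of group with NVC and WMH burden. Demographics, variant, duration of COVID-19 and vaccination are assessed as further factors by logistic regression. MCI duration is named in neither place.
- **When MCI was diagnosed.** Section 2.7 has WMH burden assessed "at baseline (at diagnosis of MCI prior to COVID-19 pandemic) and 18-month follow-up". The Fig 1 legend has "baseline MRI recorded at diagnosis of MCI prior to COVID-19 pandemic, and 18-month follow-up MRI". Section 2.10 adds "All patients enrolled have baseline MRI data with neuroradiologic report at MCI diagnosis". Section 2.5 asks only for a diagnosis of MCI and an MRI before enrolment, with no date limit in either group.
- **Time origin and end.** Visit 2 and the second MRI come 18 months after Visit 1 (2.2, 2.10). Patients with any dementia are excluded at entry (2.6).

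**The concern.** The comparison of COVID+ with COVID- patients is not randomised, so it depends on whether the groups start follow-up at a comparable point in the disease. Because dementia is excluded at entry, everyone enrolled has stayed at MCI from diagnosis to Visit 1, for a time that can differ widely between patients. That elapsed time plausibly predicts conversion over the next 18 months, in either direction: long-standing MCI may mark slow progressors, or patients further along. If its distribution differs between the groups, part of the COVID-19 coefficient reflects duration.

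The second problem does not depend on any group difference. Change in WMH burden is a term of the primary model, but it is measured over an interval that varies with MCI duration. A patient with a longer interval has had more time to accumulate WMH. The term therefore mixes rate of change with length of observation, and the Aim 4 comparison of WMH increase between groups inherits this.

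**Working it through.** **1. Is the variable absent?** Table 1, the Aim 3 list, the Aim 4 list, and the primary and covariate models of 4.2 were each checked. None contains time since MCI diagnosis. The exploratory p < 0.2 screen in 4.2 covers demographic, physiologic, cognitive and structural variables, and MCI duration is not listed under any of these.

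**2. WMH interval.** Let D be the years from MCI diagnosis (baseline MRI, per 2.10) to Visit 1. The second MRI is 1.5 years after Visit 1, so the interval is D + 1.5 years. At D = 0 it is 1.5 years; at D = 3 (assumed) it is 4.5 years, three times as long.

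**3. Does the group definition force a difference in D?** There are three readings:

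| Reading | COVID+ | COVID- | Forced gap |
|---|---|---|---|
| 2.7, Fig 1 and 2.10 taken together | MCI before the pandemic | MCI before the pandemic | none |
| 2.5 alone | no order of MCI and infection | no date limit | none |
| 2.9 read as MCI before infection, pre-pandemic wording not enforced for controls | MCI older than infection | MCI may be new | yes |

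The wording in 2.9 does not say what the diagnosis must precede, so the third reading is possible but not established.

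**4. The article's nearest figure.** It gives none for MCI duration. The planning contrast in 2.4 is 10/18 against 23/100. The odds ratio is (10 × 77)/(8 × 23) = 4.18, and the continuity-corrected chi-square gives p = 0.0108, matching the stated 0.011.

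**5. Illustration with no true COVID effect.** The only input from the article is the annual conversion rate r = 15–20% (Abstract), taken here as first-year risk. The gap, frailty variance and Weibull shape are assumptions. Let S be the proportion still at MCI after t years, with S(1) = 1 − r. The 18-month risk after d years at MCI is 1 − S(d + 1.5)/S(d).

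- *Fast converters leave first:* S(t) = (1 + θht)^(−1/θ), with θ from 0.5 to 2.
- *Hazard rises with duration:* Weibull, shape 1.3.

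| d in controls → COVID+ | False OR, frailty | False OR, Weibull |
|---|---|---|
| 0 → 2 years | 0.51–0.85 | 1.69–1.74 |
| 0 → 1 year | 0.67–0.92 | 1.42–1.45 |
| 3 → 4 years | 0.84–0.93 | 1.09–1.10 |
| no gap | 1 | 1 |

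At r = 17.5% and 0 → 2 years, the risks are 24.1% and 18.3% (frailty, θ = 1) or 27.8% and 39.8% (Weibull).

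**6. A simpler check.** Assume an odds ratio g per year of MCI duration and a gap of d years, so the false OR is g^d. Take 23% conversion in controls.

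- g = 0.8, gap 1 to 3 years: OR 0.80 to 0.51 (COVID+ rate 19.3% to 13.3%).
- g = 1.1: OR 1.10 to 1.33 (24.7% to 28.4%).
- g = 1.3: OR 1.30 to 2.20 (28.0% to 39.6%).

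To produce the whole planning odds ratio of 4.18, g would have to be 4.18^(1/2) = 2.05 with a 2-year gap, or 4.18^(1/3) = 1.61 with a 3-year gap.

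**The case against.** A reader might infer something stronger: that COVID+ patients must by definition have older MCI than controls, so that the COVID effect is confounded with MCI duration by design. The article does not support that. It needs the strict timing rule for COVID+ patients and the loose one for controls. If 2.7, Fig 1 and 2.10 apply to everyone, no control has newly diagnosed MCI and the forced gap disappears. If only 2.5 applies, nothing requires a COVID+ patient's MCI to precede the infection. In favour of the stronger reading, the planning cohort in 2.4 had MCI first and infection afterwards, and WMH change from an MRI at diagnosis can reflect COVID only if infection came later. But that planning cohort was diagnosed before the pandemic in both groups, which again removes the forced gap.

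The larger odds ratios also set every control at zero MCI duration, which nothing in the article states. With 3 against 4 years they shrink to 0.84–0.93 or about 1.1.

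Two further objections have some weight. Table 1 omits items that the study does collect (race, tobacco and alcohol use, microbleeds), so absence there does not prove the date is unrecorded, and a fuller adjustment set may exist elsewhere. MoCA, age and baseline Fazekas grade are recorded and partly reflect disease stage.

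What remains is that the article calls its list complete and names the terms of its primary model, and duration is in neither. Stage markers do not measure duration, and they do not correct the WMH interval.

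**Conclusion.** The point holds in a limited form. Time from MCI diagnosis to Visit 1 is left out of the stated variable list and the stated primary model. If that model is followed as written, any difference in MCI duration between the COVID groups is unadjusted, and WMH change is compared over unequal intervals. The interval problem follows from 2.10 and 4.2 whenever MCI durations vary between patients, whether or not the groups differ.

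It is not established that the group definition itself creates a duration difference; the timing statements in Fig 1, 2.5, 2.7 and 2.9 are not consistent enough to tell. Neither the size nor the direction of bias can be derived from the article. The calculated odds ratios show only that modest assumptions can move the estimate either way, and that the bias from a group gap vanishes when there is no gap. This is a worthwhile, inexpensive improvement to a non-randomised comparison, not evidence that the planned estimate is invalid.

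**What to change.** 1. Reconcile 2.5, 2.7, 2.9 and the Fig 1 legend on when MCI must have been diagnosed relative to the pandemic, the infection and enrolment, and state whether the rule is the same in both groups.
2. Add time from MCI diagnosis (baseline MRI) to Visit 1 to Table 1 and to the Aim 3 and Aim 4 lists.
3. Tabulate it by COVID group at baseline, so that any imbalance is visible.
4. Enter it as a prespecified covariate in the primary progression model of 4.2, outside any p-value screen. Since the WMH interval is this duration plus a fixed 18 months, the same term also accounts for the varying interval behind WMH change.

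The cost is wording in three places, one degree of freedom, and a date that should already be in the clinic record, since 2.10 says every enrolled patient has an MRI report from MCI diagnosis.

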### 2.10 Data collection process

Patients who have consented to the study are interviewed for demographic information (sex, age, race education), COVID-19 history (symptoms during infection, and symptoms without confirmed infection), COVID-19 vaccine history, medical history (oncological, genitourinary, gastrointestinal, respiratory, endocrine, neurological, cardiovascular, musculoskeletal, and psychological conditions), screened for DVA (eye surgery history, photosensitive epilepsy, glaucoma, allergies to tropicamide), and social history (previously or current use of tobacco, alcohol, and recreational drugs, and adverse childhood experiences). Medication list is obtained from all patients, and common age-related conditions (i.e., hypertension, diabetes) must be pharmacologically controlled. All patients enrolled have baseline MRI data with neuroradiologic report at MCI diagnosis. Every 6 months patients have repeat neurocognitive screening and evaluation through OUHSC Department of Neurology faculty to identify if patients have progressed from MCI to dementia. Physiologic, circulating factors, and cognitive data is obtained from patients at visit one and at 18-month follow-up. Patients are scheduled through the Department of Neurology for a second MRI to obtain neuroradiologic report at 18-month follow-up after visit one.

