## 4. Statistical analysis

### 4.1 Cross-sectional data analysis

Upon testing for normality of continuous data, independent t-test or Mann-Whitney *U* Test will be used for group comparison (COVID+ vs COVID-) and Chi-square or Fisher’s exact test for group comparison of categorical variables. Effect size will be calculated for all within and between group analyses. For **primary outcome** analysis, testing whether COVID-19 impairs NVC responses in MCI patients, fNIRS data will be analyzed using a pipeline based on General Linear Model (GLM) approach created using the Brain AnalyzIR toolbox. At the first (subject) level, regression (β) coefficients characterize NVC response and will be estimated for channels of interest in the prefrontal cortex across all n-back blocks and chromophores (HbO and HbR). At the second (group) level the GLM treats COVID status as an independent categorical factor, while the n-back block as a repeated measures factor and yields corresponding *t*-contrasts comparing NVC response within and between groups. We will test whether demographic variables, COVID-19 variants, duration of COVID-19 and vaccination influences the primary outcome through linear regression. Moreover, we will create a multivariate model using β coefficients, generated from the fNIRS pipeline, to determine whether COVID-19 predicts impairment in NVC in MCI patients. Univariate analyses of factors that may contribute to NVC impairment (i.e., age, sex, baseline structural MRI abnormalities) will be conducted, and analyses with a p value of <0.2 will be included in the multivariate model. **Secondary outcome** measures (i.e., FMD, LSCI, EEG, DVA, NIH Toolbox, circulating factors) will be compared between groups. Additionally, we will determine whether history of COVID-19 contributes to impairment in functional cognitive measures (i.e., n-back, NIH Toolbox) by multiple and simple linear regression. For **exploratory analyses**, we will determine whether group (COVID+ vs COVID-) alters the relation between NVC and peripheral, cognitive, and structural measures through multiple regression. Correlations for these variables will be performed within groups to determine strength of relationship with NVC.

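### The endothelial outcomes of Aim 1 are compared between non-randomised COVID-19 groups without adjustment, and tobacco use, although collected, enters no variable list or named model

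*Protocol article*

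**What the plan says.** Section 2.10 lists what is asked of each consenting patient. It includes "social history (previously or current use of tobacco, alcohol, and recreational drugs, and adverse childhood experiences". It also says: "Medication list is obtained from all patients, and common age-related conditions (i.e., hypertension, diabetes) must be pharmacologically controlled". Drug-treated patients are therefore expected in the cohort.

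Section 2.9 introduces its table with "All variables included in the study are represented in" Table 1. The table has no row for tobacco and none for medication. The nearest row is Comorbidities, defined as "Past medical history and/or ongoing medically controlled for conditions". The Aim 1 list names the vascular, EEG and blood measures and ends with "antioxidant capacity, COVID-19 status, SARS-CoV-2 variants, time since infection, and vaccination history".

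Section 4.1 names an independent t-test or Mann-Whitney test for continuous data. Of the secondary outcomes it says that these "measures (i.e., FMD, LSCI, EEG, DVA, NIH Toolbox, circulating factors) will be compared between groups". Covariates are named only for other outcomes. For the NVC model: "Univariate analyses of factors that may contribute to NVC impairment (i.e., age, sex, baseline structural MRI abnormalities) will be conducted".

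**The concern.** Aim 1 asks whether a history of COVID-19 disrupts systemic endothelial function. That is a causal question put to groups formed by infection history, not by randomisation. Smoking, age, sex, comorbidity and treatment can each plausibly move brachial dilation, skin perfusion, retinal reactivity and inflammatory markers.

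The protocol accepts this kind of influence elsewhere. Section 3.2.1 compares blood pressure between groups because a difference might affect the vascular measurements, section 3.2.6 records skin temperature around LSCI, and the Discussion says that COVID-19 effects must be separated from medical history and comorbidities. For FMD, LSCI and the circulating factors, section 4 contains no step that does so.

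At stake is the reading of the Aim 1 endothelial results. A difference in patient mix could be reported as an effect of infection, although data that would reduce this risk are already being collected.

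**Working it through.** **1. Tracing the two items through the plan**

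| Place | Tobacco | Medication |
|---|---|---|
| 2.10, interview | collected | collected |
| Table 1 | no row | no row; Comorbidities is a partial proxy |
| Aim 1 list (2.9) | absent | absent |
| 4.1, FMD, LSCI, DVA, circulating factors | no covariates stated | no covariates stated |
| 4.1, NVC regressions | not named | at most through Comorbidities, which Table 1 labels Demographic |
| 4.2, secondary outcomes | compared within and between groups, no covariates stated | same |
| 4.2, dementia regressions | not named | at most through Comorbidities |

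The other regressions in 4.1 have cognition as the outcome, or explore how group alters the relation of NVC to other measures. None is an adjusted model of COVID status on an endothelial outcome.

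**2. Size, by illustration**

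The plan gives no figure to reproduce. All inputs here are assumptions, apart from the ceiling of 200 patients and the 10% dropout in section 2.4, which give 200 × 0.9 = 180.

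- Effect of one omitted yes/no factor on the outcome: 0.3 to 0.5 SD.
- Difference in its prevalence between groups: 10 to 20 percentage points.
- Bias per factor = prevalence difference × effect: 0.10 × 0.3 = 0.03 SD to 0.20 × 0.5 = 0.10 SD.
- Two factors in the same direction: 2 × 0.03 = 0.06 SD to 2 × 0.10 = 0.20 SD.

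For a two-sided 5% test with group sizes n1 and n0, the non-centrality is bias × √(n1·n0/(n1+n0)). The rejection rate under a true null is Φ(nc − 1.96) + Φ(−nc − 1.96). For 90 vs 90 the multiplier is √45 = 6.71.

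| Bias (SD) | nc, 90:90 | Rejection, 90:90 | Rejection, 60:120 | Rejection, 27:153 |
|---|---|---|---|---|
| 0.03 | 0.20 | 5.5% | 5.4% | 5.2% |
| 0.06 | 0.40 | 6.9% | 6.7% | 6.0% |
| 0.10 | 0.67 | 10.3% | 9.7% | 7.7% |
| 0.20 | 1.34 | 26.9% | 24.4% | 16.0% |

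The 27:153 split applies the 18:100 ratio of the data cited in section 2.4 to 180 patients (180 × 18/118 ≈ 27). At Visit 1 no dropout need have occurred; with 100 vs 100 the range from 0.06 to 0.20 SD becomes 7.1% to 29.3%.

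**3. Smoking alone**

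Assume 15% smokers in the COVID- group, 5 to 20 points more in the COVID+ group, and an effect of 0.3 to 0.8 SD. The bias is 0.05 × 0.3 = 0.015 SD to 0.20 × 0.8 = 0.16 SD. Allowing for the extra variance from smoking, rejection of a true null is 5.1% to 17.4% at 90:90 and 5.1% to 15.9% at 60:120.

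**The case against.** **Condensation.** This is a journal article, and covariate sets for secondary outcomes are often left to an analysis plan that is not shown. That would excuse silence. Here, however, the test for these outcomes is named and it is an unadjusted one, so the point concerns a stated method.

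**Table 1 as a complete list.** A reader might infer from section 2.9 that anything absent from Table 1 has been barred from analysis. The documents do not support that. The caption calls the table a summary, and race, microbleeds and LSCI skin temperature are also recorded or assessed without a row. Likewise the Aim 1 list omits age and sex, which section 4.1 nevertheless screens for the NVC model. Absence from these lists is corroboration; the weight rests on the comparison in section 4.1.

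**Medication left out of every model.** This too goes further than the text. Comorbidities covers medically controlled conditions, is labelled Demographic, and could enter the regressions on demographic variables. The candidate list for NVC may also be meant as examples. So treatment is partly captured for NVC and dementia, though without drug class and not for FMD, LSCI or circulating factors. Tobacco has no such proxy.

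**Existing safeguards.** Uncontrolled disease is excluded and blood pressure is compared between groups. Neither step balances smoking, and controlled disease often means treated disease.

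**Adjusting for medication.** Drug use is recorded at the study interview, after infection in patients with a COVID-19 history. If infection leads to vascular disease that is then treated, drug use lies downstream, and adjusting for it could remove part of the effect sought. This objection stands and shapes the fix.

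**Conclusion.** The point holds in a limited form. As written, the group comparison of FMD, LSCI, DVA and circulating factors is open to confounding by smoking, and equally by age, sex, comorbidity and pre-infection treatment. No other section adjusts the endothelial outcomes.

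It would be too strong to say that such differences will be attributed to COVID-19. That happens only if the groups differ on these factors, and the documents contain nothing on whether they do. The range of about 7% to 27% depends on two factors acting in the same direction, on the assumed effects and prevalence differences, and on an equal split that the plan does not state. At 27:153 it falls to about 6% to 16%, and one weak factor leaves the error rate close to 5%.

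This is a worthwhile, low-priority improvement to the Aim 1 analysis. It does not invalidate the study.

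**What to change.** - Add smoking status (never, former, current) to Table 1 and to the Aim 1 list.
- In section 4.1, replace the plain comparison of FMD, LSCI, DVA and circulating factors with a prespecified linear model of COVID status adjusted for age, sex, smoking and comorbidities, on a transformed scale where an outcome is skewed. The covariates should be fixed in advance, not selected at p < 0.2. The unadjusted comparison can be reported beside it.
- Use medication class only in a sensitivity analysis, or restrict it to drugs started before infection, and state the reason.

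The cost is the coding of data already collected, revised wording in Table 1 and section 4, and a few degrees of freedom out of up to 200 patients. Adjustment reduces bias from the listed factors only; unmeasured confounding remains, as the Discussion acknowledges.
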